**Figure 1. f1:**
[figure not shown]
Geographical location of study. Note: This figure was adapted from the original image (
NordNordWest, 2019). This image is free to use under the creator’s licensing conditions. Licensing agreement available at
https://creativecommons.org/licenses/by-sa/3.0/de/legalcode.

In each of the three Palikas, we selected one ward (the administrative unit below a Palika) as a treatment site, and chose a clinic in the ward based on our desire to maximize geographic diversity across the three Palikas. Treatment facilities were selected purposively based on relative need for immunization and service delivery support and willingness to collaborate, as the intervention design and implementation would require the input and participation of local stakeholders. We considered other designs (including a cluster randomized study) but decided against it for two reasons. First, it would be hard to justify a random sample when the number of units (in this case Palikas) is only six. Second, we were constrained by resources to expand to more than three intervention Palikas. Given these constraints, it was deemed more useful to choose sites based on specific criteria. For example, for each ward in the treatment arm, we selected another ward and clinic as a control site in that Palika, matched on population characteristics including ethnicity, age distribution, gender ratio, and population size with the treatment ward. Each control facility is located in a separate geographic vicinity from the treatment facility in its Palika to minimize contamination.

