### Research design and intervention

This study is composed of three phases: 1) qualitative formative assessment, 2) intervention implementation, and 3) quantitative impact assessment (see
Figure 2). Mixed methods approaches can be useful for producing a more comprehensive picture of the issue at hand and building on initial findings (
Denscombe, 2008). For this study, the formative assessment will be used to understand individual and group perspectives of immunization practices in their communities and opinions about their local health facilities. The findings from this assessment will be used to build on the Rejoice Architecture intervention plan, which will include improvements to the treatment health facilities through three basic components: 1) physical environment and infrastructure, 2) social environment and communication with health staff, and 3) systems management and scheduling. Specific intervention activities in the first component may include painting walls, providing furniture, adding greenery, constructing a covered outdoor waiting area, and displaying educational and entertaining videos on a television screen. For the second component, we may design a client-provider communication checklist and facilitate a workshop on interpersonal communication with clients and caregivers. For the third component, the intervention may involve implementing an appointment reminder system for caregivers and refining the health facility’s patient scheduling system. Activities will be refined, expanded upon, or added based on priorities identified in the formative assessment. Health facilities in the control group will receive no intervention components and will provide care as usual. Following the formative assessment, a clustered quasi-experimental survey design will be utilized to determine overall impact of the intervention by comparing outcomes between health facilities which received the intervention and those which did not.

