### Study design

We will use a clustered quasi-experimental design with panel data to measure the impact of the intervention on immunization behaviors, intent to vaccinate, and uptake of other health services. Participants from each of the six study sites will complete a baseline survey preceding intervention implementation and an end-line survey approximately eight months later. Data collectors will read questions aloud to participants and then record responses on a handheld tablet. Surveys are available as
*Extended data* (
[name], 2020).

In addition, the physical conditions of the health facilities and immunization centers will be assessed using checklists at baseline. These checklists will be used to corroborate subjective reports from interviews, focus group discussions, and surveys and assist with identifying needed resources to include in the intervention design. Our data collectors will visit each health facility and the surrounding immunization centers on the designated “Immunization Day” to complete the checklists.

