### Quantitative

The primary objective of the quantitative analysis is to determine whether the Rejoice Architecture intervention results in greater vaccination uptake (or intentions for vaccination) among mothers (or prospective mothers) in the treatment, compared to the control, arm. Hierarchical linear regressions (HLM) will be used to test the primary hypothesis that vaccination rates (number of newborns vaccinated divided by total live births within a catchment area) in the treatment group will be significantly greater (goal is 10 percent) than that in the control group. This analysis will take into account the clustered nature of data within each of the six catchment areas (three in treatment and three in control areas).

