### Limitations

This study may be limited in several ways. For instance, the study sites were selected purposively and are in one of 77 districts in Nepal; therefore, generalizability could be limited. Findings may also be limited to rural settings among certain ethnic groups in Makwanpur and may vary among other geographic or ethnic contexts.

Considering the current COVID-19 pandemic, intervention implementation may be delayed, and data will likely reflect the pandemic’s effects on facility closures, attitudes toward help-seeking, and health-related behaviors. However, both treatment and control facilities will be exposed to the virus and Nepal’s national response, and so no significant differences due to COVID-19 are expected between groups.

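### The primary test is worded as a treatment-versus-control difference in vaccination level, with no baseline term, although treatment facilities were chosen on need and a baseline survey exists

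*Protocol article*

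**What the plan says.** The Quantitative part of Data analysis states the primary hypothesis as a comparison of levels: vaccination rates "in the treatment group will be significantly greater (goal is 10 percent) than that in the control group". The rate is defined there as "vaccination rates (number of newborns vaccinated divided by total live births within a catchment area", with the bracket closing at that point. The model is a hierarchical linear regression, and the only design feature it is said to handle is clustering: "This analysis will take into account the clustered nature of data within each of the six catchment areas". Research design and intervention describes impact in the same way, as "comparing outcomes between health facilities which received the intervention and those which did not".

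Study setting explains how the arms were formed: "Treatment facilities were selected purposively based on relative need for immunization and service delivery support and willingness to collaborate". For each treatment ward a control ward and clinic were taken in the same Palika, "matched on population characteristics including ethnicity, age distribution, gender ratio, and population size with the treatment ward". Immunization coverage is not in that list.

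The Study design section under Quantitative methods calls the data a panel meant to measure impact. Participants at all six sites "complete a baseline survey preceding intervention implementation and an end-line survey approximately eight months later". Contribution to the field reports that baseline data have been collected.

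Limitations draws one consequence from the selection of sites: "the study sites were selected purposively and are in one of 77 districts in Nepal; therefore, generalizability could be limited".

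**The concern.** Without randomization, a difference in end-line level is the intervention effect plus whatever difference was there at the start. Here the start is unlikely to be equal by design. One selection criterion, need for immunization support, bears directly on the outcome, and the other, willingness to collaborate, plausibly does. The matching named is demographic. A cluster term in the model widens the standard error for chance variation between wards, but it does not remove a systematic difference between arms.

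The conclusion of the study is at stake in both directions. If the needier facilities start lower, a real gain may go undetected. If the willing facilities start higher or are already improving, a gain may be reported that the intervention did not produce. The study collects the data that could address the difference in starting level, but the stated test does not use them.

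**Working it through.** **Inputs.** From Sampling: 83% rising to 93%, alpha 0.05, power 80%, intraclass correlation 0.01, 380 per arm, 20% attrition, 950 at baseline, six clusters. From Data analysis, Quantitative: three clusters per arm. Two-sided testing is assumed, because it reproduces the stated size.

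**Step 1: the plan's own figure.**
- Individuals per arm: [1.96·√(2·0.88·0.12) + 0.842·√(0.83·0.17 + 0.93·0.07)]² / 0.10² = 164.6, so 165.
- Design effect at 380/3 = 126.7 women per cluster: 1 + (126.7 − 1)·0.01 = 2.257.
- 165 × 2.257 = 372 per arm, within 3% of the stated 380.
- Attrition: 760 / 0.80 = 950, exact.
- Effective size at 380 per arm: 380 / 2.257 = 168.4. Power = Φ[(0.10 − 1.96·0.0354) / 0.0350] = Φ(0.87) = 80.9%.

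So the study is sized for a simple contrast of 83% with 93%. For an end-line comparison, that requires both arms to start at the same rate.

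**Step 2: a baseline gap, as illustration.** The protocol gives no gap. Assume control at 83% throughout, no secular trend, a true effect of +10 points and an effective size of 168.4 per arm. With treatment starting g points lower, the end-line difference is 10 − g.

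| Treatment starts lower by | End-line difference | Power |
|---|---|---|
| 0 | +10 | 81% |
| 3 | +7 | 47% |
| 5 | +5 | 26% |
| 8 | +2 | 7% |
| 10 | 0 | 2.5% |

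For g = 5 the rates are 88% and 83%: Φ[(0.05 − 1.96·0.0384) / 0.0383] = Φ(−0.66) = 25.5%.

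Now take no true effect and treatment starting higher. A 3-point advantage gives a significant result favouring treatment about 11.5% of the time, and a 5-point advantage 25.5%, against a nominal 2.5%.

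The 5-point cases show the difficulty plainly. A true gain of 10 from a 5-point deficit and no gain from a 5-point advantage both end at 88% against 83%. A comparison of end-line levels cannot tell them apart. A comparison of changes gives +10 in one and 0 in the other, provided the arms would otherwise have moved in parallel.

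These figures use normal critical values and so make no allowance for the few degrees of freedom that three clusters per arm leave.

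**Step 3: which baseline is available.** The tested quantity is a catchment ratio of vaccinated newborns to live births, and no baseline measurement of it is described. The survey does measure immunization behavior at both times, but Instruments gives those items to mothers of children under 2 and gives intention items instead to pregnant women and prospective mothers. From Table 2, mothers number 300 + 300 = 600 and the others 100 + 250 = 350. A within-woman change in behavior is therefore available for 600 of the 950.

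**The case against.** The strongest reply is that the baseline is unmentioned rather than excluded. The Study design section says panel data will measure impact, Sampling speaks of an increase in rates and inflates for attrition because of the panel, and a hierarchical model can carry repeated measures. A condensed article may leave model terms to an analysis plan. This stands in part: a reader might infer that the investigators have decided to ignore the baseline, and the text does not say so. But the article does state its primary contrast, as a difference in level, and describes impact in the same way elsewhere. That is a stated choice at odds with the panel design, and the passages need reconciling.

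A reader might also infer that the bias would inflate the effect. Selection on need points the other way, and the net sign is unknown.

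A reader might add chance imbalance between wards: √(2·0.01·0.83·0.17/3) = 3.1 points, or about ±6. That should not be counted here. Its variance, 0.00094, is already part of the 2·0.1411/380·2.257 = 0.00168 implied by the design effect (the remaining 0.00074 is between individuals), and the clustering adjustment covers it. It is sampling error, not bias.

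Three smaller points stand. The need criterion is applied to facilities and covers service delivery as well as immunization. The matching list is introduced as a partial one. Pairing within Palika removes some differences between areas.

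**Conclusion.** The concern holds. As worded, the primary test passes any baseline difference in coverage point for point into the estimate, in a design where facilities were selected partly on need and no matching on coverage is stated. The sign is unknown, and the size cannot be derived from the protocol. The 5-point illustrations (power of about 26% instead of 81%, or about a 26% chance of a significant result favouring treatment when there is no effect) rest on an assumed gap and on no secular trend. They show sensitivity and do not predict what will happen.

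Limitations presents purposive selection as a matter of generalizability only; it is also a threat to internal validity. Nor do the documents support the reading that the tested outcome can simply be differenced from data in hand: no baseline for the newborns-to-live-births ratio is described.

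**What to change.** Before end-line data are seen, reconcile the Quantitative analysis paragraph with the panel design:

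- Make the primary estimate baseline-adjusted, on the survey immunization-behavior outcome among mothers of children under 2. Use either an arm-by-time term (difference in differences) or adjustment for baseline status or baseline ward coverage, with Palika pair in the model. Name one of these as primary.
- Analyse intention in the same way among pregnant women and prospective mothers.
- Keep the newborns-to-live-births rate as the primary outcome only if a baseline value for it is obtained in all six catchments.
- Report the baseline gap for each Palika pair.
- State in Limitations that purposive selection also threatens internal validity, including regression to the mean in facilities chosen for need.

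No new survey is needed, but the change is more than wording. The primary outcome must be tied to the survey measure, and the behavior analysis rests on about 600 women, or 600 × 0.80 = 480 (240 per arm) after the planned attrition. At that size the design effect is 1 + (80 − 1)·0.01 = 1.79, the effective size 240/1.79 = 134 per arm, and a plain 83% versus 93% contrast has Φ[(0.10 − 1.96·0.0397)/0.0392] = about 71% power. Power for a change analysis depends also on the within-woman correlation, which the protocol does not give, so it should be computed under a stated range. Parallel trends remain an assumption and regression to the mean a limitation, and with three clusters per arm neither can be tested well.

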## Introduction

 Communicable diseases constitute a global health threat, with low- and middle-income countries experiencing the greatest burden (
The World Medical Association, 2020). Each year, 1.5 million people die from vaccine-preventable diseases, 600,000 of whom are children under the age of 5 (
Gavi, 2020). Immunization is an effective way to prevent disease and save lives, with two to three million lives saved by vaccines every year (
World Health Organization, 2019). Individuals benefit from immunization through illness prevention, reduced healthcare costs, and greater productivity for themselves and their caregivers (
Gavi, 2020;
Njau & Cairns, 2016;
Ozawa *et al.,* 2012). Children, who are often at greater risk of morbidity and mortality from communicable disease, experience greater cognitive ability, physical strength, and school performance when they receive vaccines (
Gavi, 2020;
Nandi & Shet, 2020). Immunizations also contribute to improved community health through herd immunity and greater economic stability from long-term cost savings (
Fox *et al.,* 1971;
Gavi, 2020;
Ozawa *et al.,* 2012;
Ozawa *et al.,* 2017). 

Currently, nearly 20 million children worldwide younger than one year old have not received the minimum basic vaccines they need to live long, healthy lives; 77% of which represent children living in Gavi-supported countries (
Gavi, 2020). Furthermore, only 17% of children under 1 have received the full dosage recommended by the World Health Organization (
Gavi, 2020). This coverage gap is present in Nepal, where only 78% of children between 1–2 years have received all recommended vaccines (
Ministry of Health Nepal *et al.,* 2017). It is important to note, though, that while the majority of children receive their vaccines by the age of 2, only 43% receive them at the age-appropriate times for which they are scheduled (
Ministry of Health Nepal *et al.,* 2017). Moreover, immunization coverage is highly variable in Nepal, with rates ranging from 65% in some provinces to 93% in others (
Ministry of Health Nepal *et al.,* 2017). Coverage is dependent on the specific vaccine as well, ranging from 73% for the first dose of the Pneumococcal vaccine to 98% for the Bacille Calmette Guerin (BCG) vaccine (
Ministry of Health Nepal *et al.,* 2017). These data demonstrate a critical need to ensure consistent and comprehensive coverage of immunization, including in Nepal.

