## Methods

### Study setting

The study is being conducted in three Palikas (equivalent to a municipality) of the Makwanpur District of Nepal: Thaha Municipality, Kailash Rural Municipality and Bakaiya Rural Municipality (see
Figure 1). Makwanpur District is one of 77 districts in Nepal with a population of 420,477 (
Central Bureau of Statistics, 2014). Makwanpur District was selected as the study area for this project for a number of reasons, including its immunization rate, geographic location, and demographic diversity. As of 2017, the rate of immunization coverage of children under one year in Makwanpur is 76.7%, comparable to Nepal's overall immunization rate of 73.1% (
Ministry of Health Nepal Department of Health Services, 2018). Additionally, Makwanpur has a geographical range which reflects the three regions of Nepal with an altitude of 2,488 meters in the northern parts and 166 meters in the southern parts. The three selected municipalities were chosen to represent Nepal’s three regions of the mountains (Thaha Municipality), hills (Bakaiya Rural Municipality) and terai (lowlands; Kailash Rural Municipality). Additionally, Makwanpur is 76.7%, comparable to Nepal’s overall immunization rate of 73.1% (
Ministry of Health Nepal Department of Health Services, 2018). Furthermore, Makwanpur is accessible from Kathmandu, the capital of Nepal, and is large in size (approximately 2,426 km2 or 1.6% of the total land area of Nepal;
Central Bureau of Statistics, 2014). These geographical features make Makwanpur an ideal candidate setting to maximize feasibility and minimize contamination. Makwanpur also represents much of Nepal’s diverse population, including 78 ethnic groups with various cultures and languages spoken (
Central Bureau of Statistics, 2005).

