### Sampling

Like the qualitative methods, FCHVs from each ward will assist in identifying women in the community who fit the eligibility requirements. With their list of names and locations, data collectors will randomly select houses for recruitment. The target sample size is
*n* = 950 (treatment = 475, control = 475) with an anticipated attrition rate of 20%. This was determined by assuming an increase in vaccination rates from 83% (2019 estimate) to 93% (envisioned), an alpha level of 0.05 and power of 80%, and data collection from 6 clusters. To estimate the vaccination rate in Makwanpur in 2019, we assumed an increase of approximately 6% from 2017, when the data were last reported, based on antigen coverage trends from 2014 to 2017 (
Ministry of Health Nepal Department of Health Services, 2018). We estimate an intraclass correlation of 0.01, making the required sample size 380 in the treatment and 380 in the control groups. However, because this is a panel design, we envision an attrition rate of 20%, which brings our sample size at baseline to 950. We will sample four cohorts of women with children younger than one year, women with children between 1–2 years, women who are pregnant at baseline, and prospective mothers. We anticipate greatest availability of women in the first two cohorts, and the least availability of pregnant women, which we expect will create variation in our sample sizes between cohorts. For the complete anticipated sampling breakdown, see
Table 2.

**Table 2. T2:** Breakdown of quantitative data collection by treatment and control facilities.

Participant	Control	Treatment	Total
Women with children <1 year	150	150	300
Women with children 1–2 years	150	150	300
Pregnant women	50	50	100
Prospective mothers	125	125	250
Total	475	475	950

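### The stated 80% power depends on normal quantiles with only six wards: at the plan's own inputs it is about 58% unpaired or 36% paired, and the plan does not say whether the ICC of 0.01 covers differences between the matched Palikas.

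*Protocol article*

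**What the plan says.** All references are to the Protocol article.

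- **Study setting.** Of the three Palikas: "The three selected municipalities were chosen to represent" mountains, hills and terai. Within each, one treatment ward was chosen, and then "we selected another ward and clinic as a control site in that Palika, matched on population characteristics". The design is therefore three within-Palika pairs. The sentence explaining why randomisation was rejected counts six Palikas, although the same section names three Palikas with two wards each.
- **Quantitative methods, Sampling.** The calculation assumes "an increase in vaccination rates from 83% (2019 estimate) to 93% (envisioned), an alpha level of 0.05 and power of 80" percent, with "data collection from 6 clusters". It continues: "We estimate an intraclass correlation of 0.01, making the required sample size 380 in the treatment and 380 in the control groups". Allowing for 20% attrition gives 950 women at baseline. No source is given for 0.01, and nothing says whether it is a total or a within-Palika value.
- **Data analysis, Quantitative.** The primary test is a hierarchical linear regression. On clustering: "This analysis will take into account the clustered nature of data within each of the six catchment areas", three per arm. Neither a Palika or pair term nor a baseline adjustment is mentioned.
- **Contribution to the field.** The baseline survey has been collected and the intervention has not started.

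**The concern.** The design has a pair structure that neither the sample size nor the described analysis mentions. Each Palika gives one ward to each arm, so Palika differences cancel from the treatment contrast if the pairs are modelled. If not, they stay in the between-ward variance and widen its standard error. Whether the single ICC leaves room for them cannot be told from the text.

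The firmer problem applies whichever model is used. Treatment was assigned to wards, and there are three per arm. The between-ward variance must be estimated from six wards, which leaves 4 df for an unpaired comparison and 2 for a paired one. A power figure taken from normal quantiles treats that variance as known. At stake is whether a null result could be read as evidence that the intervention does not work.

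**Working it through.** **Inputs.** From Sampling: 83% and 93%, alpha 0.05, power 80%, six clusters, ICC 0.01, 380 per arm. Two-sided testing is my assumption, since the plan does not state it; the one-sided variants (227 or 294 per arm) do not reproduce 380. Women per ward: m = 380/3 = 126.7. The comparison is taken as unadjusted at end-line.

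**1. The plan's own figure.** Two independent proportions need 165 per arm. The design effect is 1 + (126.7 − 1) × 0.01 = 2.257, and 165 × 2.257 = 372.4, so 373 against the stated 380. Effective size is 380/2.257 = 168.4 per arm, with power 80.9%. Attrition: 380/0.8 = 475 per arm, 950 in total. The figure reproduces.

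**2. Standard error of the arm difference.** The mean binomial variance is (0.83 × 0.17 + 0.93 × 0.07)/2 = 0.2062/2 = 0.1031.

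- Variance of a ward proportion: 0.01 × 0.1031 + 0.99 × 0.1031/126.7 = 0.001031 + 0.000806 = 0.001837.
- SE = √(2 × 0.001837/3) = 0.0350, so 0.10/0.0350 = 2.858.
- Normal quantiles: Φ(2.858 − 1.960) = 81.5%.

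**3. Same SE, ward-level df (noncentral t).** The detectable difference is the one with 80% power, holding the variance at the planned rates.

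| Comparison | Critical value | Power for 10 points | Detectable difference |
|---|---|---|---|
| Normal quantiles | 1.960 | 81.5% | 2.80 × 3.50 = 9.8 points |
| Unpaired, 4 df | 2.776 | 58% | 3.76 × 3.50 = 13.2 points |
| Paired, 2 df, 0.01 within Palika | 4.303 | 36% | 5.65 × 3.50 = 19.8 points |

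From 83%, the largest possible rise is 17 points.

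**4. If 0.01 is the within-Palika ICC and Palikas vary on top of it.** The documents give no between-Palika variance, so the SDs are assumed. SE = √(2 × (0.001837 + SD²)/3).

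| Palika SD (points) | Total ICC | SE (points) | Unpaired, normal | Unpaired, 4 df | Paired, 2 df |
|---|---|---|---|---|---|
| 0 | 0.010 | 3.5 | 81.5% | 58% | 36% |
| 2 | 0.014 | 3.9 | 74% | 50% | 36% |
| 3 | 0.019 | 4.3 | 65% | 43% | 36% |
| 5 | 0.033 | 5.4 | 46% | 30% | 36% |

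With t quantiles, pairing gains power only above a Palika SD of about 4 points.

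**5. If 0.01 is already the total ICC.** Unpaired power stays at 81.5% (normal) or 58% (4 df). Paired power on 2 df runs from 36%, with none of the ICC due to Palikas, to 62% with all of it.

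**6. How much margin the ICC leaves.** With three wards per arm, the variance of the difference cannot fall below ICC × 0.2062/3, however many women are surveyed. For 80% power with normal quantiles the ICC must stay below 3 × (0.10/2.802)²/0.2062 = 0.0185. On 4 df the limit is 3 × (0.10/3.761)²/0.2062 = 0.0103, almost the assumed value itself. An ICC of 0.01 corresponds to a between-ward SD of √(0.01 × 0.1031) = 3.2 points.

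**The case against.** **The ICC may already include Palika differences.** In a six-cluster unpaired calculation an ICC nominally covers all variation between catchments. This stands. A reader might infer that 0.01 excludes Palika variance, so that true power is 46% or less even with normal quantiles. The text does not support that; it says nothing either way.

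**The Introduction's coverage figures look like evidence of wide spread** ("with rates ranging from 65% in some provinces to 93% in others"). They compare provinces across Nepal, whereas the three Palikas lie in one district, so they say nothing about Palika spread.

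**Adding a Palika term could make matters worse.** This also stands. It costs 2 of 4 df, and at the stated inputs the paired test is the weaker one. Dropping a match with so few pairs is a defensible choice. Omitting the term causes no bias and no excess type I error from that source; it costs only precision.

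**Baseline data could help.** The same women are surveyed twice, so baseline adjustment could remove stable Palika differences and raise power above the figures here. The described analysis states no such adjustment, and it would not add wards.

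**The article is condensed and the analysis plan is not shown.** Silence on a Palika term is therefore not an error. But the 80% claim and its inputs are printed here, and the claim can be checked.

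**A mixed model may be tested with normal quantiles anyway.** That does not rescue the figure: referring a statistic with 4 df to 1.96 gives a two-sided error of about 12%, not 5%.

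**Conclusion.** The power statement is wrong as written. Its arithmetic reproduces, but only by treating the between-ward variance as known. With six wards and the plan's own inputs, power is about 58% unpaired. Paired, it is about 36% if 0.01 is the within-Palika ICC, and at most 62% if 0.01 is the total ICC and entirely due to Palikas. No version reaches 80%. These figures assume two-sided testing, 380 women per arm analysed, and no baseline adjustment.

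The design and the description of clustering do not match: three pairs in one place, six catchments in the others, with an ICC that is neither sourced nor defined. If Palikas vary beyond 0.01, unpaired power falls further, by an amount the documents cannot fix. It would go too far to conclude that the ICC omits Palika variance or that a Palika fixed effect is clearly better. The first is not stated, and the second depends on a Palika SD that is unknown.

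**What to change.** 1. In Sampling, restate power or the detectable difference with small-sample df over a range of ICCs, for example 0.01 to 0.03. Say whether 0.01 is a total or a within-Palika value and give its source.
2. Check it against the baseline survey already collected. This can only be rough: with three Palikas, a 95% interval for the Palika SD runs from about 0.5 to 6.3 times the estimate even ignoring ward noise, so it cannot settle whether pairing pays.
3. Before end-line data are seen, fix whether the primary model carries the Palika pairs and acknowledge the loss from 4 to 2 df if it does. State the df used for the test.
4. Report the three within-Palika treatment-control differences beside the pooled estimate.
5. In Study setting, change the count of six from Palikas to wards.

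This takes a few sentences and one recalculation, with no new data collection. The downside is a less favourable stated power.
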